**CLEAN Meds RCT: Carefully seLected and Easily Accessible at No charge Medications**

Canada is the only high income country where health care services are publicly funded for the general population but medications are not.[1] We propose an RCT of providing carefully selected, essential medications at no charge (compared with usual medication access) to primary care patients. The impact of this intervention on appropriate medication adherence, valid surrogate health outcomes and costs will be determined:

**Population** – Adult primary care patients who report cost-related non-adherence to medications

**Intervention** – Free and convenient access to a carefully selected set of essential medications with otherwise usual care (n = 392)

**Control** – Usual access to medications and usual care (n = 392)

**Outcome** – *Primary*: Appropriate adherence to medications over 12 months. *Secondary*: HbA1c levels (in patients with diabetes); blood pressure (in hypertensive patients); cholesterol (in patients with dyslipidemia); average per person medication costs.

***1. The Need for a Trial******1.1 What is the problem to be addressed?***

A large number of different medications are prescribed in Canada and a much larger number of Canadians do not take prescribed medications because of the cost. The intervention in this trial – the free provision of a carefully selected set of medications – has the potential to address both medication selection and medication adherence.

Medication adherence is an important determinant of health outcomes.[2] Approximately one half of treatments for chronic disease are not taken as directed.[3] Cost is one of several important causes of poor adherence and it is particularly important for vulnerable people.[4, 5] At least 2.4 million adult Canadians report cost related nonadherence to medications.[5] 31 % of prescriptions in Quebec are not filled and those of highest cost are least likely to be filled.[4] Providing full drug coverage may improve medication adherence and clinical outcomes, particularly for vulnerable individuals and those with chronic diseases.[6]

The size of many Canadian formularies such as the Ontario Drug Benefit Formulary, which contains over 3800 medications[7], makes it difficult for clinicians to know the safest and most effective medications to prescribe. This may partially explain poor medication selection. For example 16% of older Canadian primary care patients receive at least one potentially inappropriate medication.[8] 17% of NSAID prescriptions are for diclofenac[9] even though it is associated with additional vascular risk compared to other NSAIDs such as naproxen and has no advantage.[10] Inappropriate prescribing has been linked to excess morbidity and hospitalization.[8]

Approximately 12 billion dollars are spent each year by provincial and territorial governments on medications in Canada.[11] From 2000 to 2010, the annual average per capita growth in prescription expenditures in Canada was approximately 4%. [1] In contrast, comparable countries such as the United Kingdom only experienced growth approximating 1%. [1] The large number of medications in formularies may contribute to the high prices of medications in Canada. Medication costs are lower in countries such as Sweden with limited formularies (similar to the list of essential medications that will be employed in this study).[12] Per capita medication costs in 2011 for Canada and Sweden were \$771 and \$477,

respectively.[13] Multiple national reports over several decades have concluded that a national pharmacare system would save billions of dollars annually from a societal perspective[1, 14, 15] yet provincial decision makers have cited cost considerations in deciding against making large formularies containing thousands of medications[7] available to all residents.[1] The use of a carefully selected set of medications might be dramatically less expensive, yet still provide the general population with access to the majority of medications they need.

Access to medications is dependent on local pharmacies. In Canada, the current dispersion of dispensing over multiple pharmacies is associated with a greater risk of severe adverse drug reactions in the elderly.[16] This may be due to incomplete communication among prescribers and dispensing pharmacists.[16] The use of an integrated prescriber-pharmacist medication dispensing system has showed great promise. In this system, the clinician and pharmacist both have access to the electronic medical record where prescriptions are entered. The pharmacist dispenses medications by mail to the patient and provides counseling over the telephone. Observational studies have demonstrated that medication adherence and efficiency are greater when patients are mailed prescription medications.[17-21] Observational studies have also found an association between mailing prescription medications and fewer emergency room visits[22] and better management of dyslipidemia.[23]

An intervention that combines three critical elements – free access, a carefully selected set of medications, and centralized distribution and mailing – is a logical focus for a randomized controlled trial that would provide important information for policy makers. Other short evidence-based lists of medications have been developed, but trials have demonstrated that merely educating clinicians about medication lists does not change practice or the medications patients actually receive.[24] In this intervention, prescribing will be driven to the selected medications because patients will have access to these medications at no expense. It would be impractical and expensive to give patients access to thousands of different medications at no charge; a short list of medications couples naturally with centralized medication distribution for this trial and is easily scalable if the trial results are positive. The individual components of the intervention could also be trialed if the results of this trial are positive.

### *1.2 What are the principal research questions to be addressed?*

Primary question: Does providing convenient access to a carefully selected set of essential medications for free to adult primary care patients increase appropriate medication adherence?

#### *Secondary questions:*

Does providing convenient access to a carefully selected set of essential medications for free to adult primary care patients :

- 1) Increase appropriate prescribing?
- 2) Increase treatment adherence (regardless of whether prescriptions are appropriate)?
- 3) Improve HbA1c levels in patients with type 2 diabetes on oral hypoglycemic medications?
- 4) Improve blood pressure control in hypertensive patients on antihypertensive medications?
- 5) Improve LDL cholesterol levels in patients taking a statin?
- 6) Reduce per capita medication costs?

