#### *1.6 Describe any risks to the safety of participants involved in the trial.*

Patients in the intervention group will have improved access to the medications on the list of essential medications but retain their usual access to all medications (i.e., they can choose to pay for medications that are not on the list). Thus access is not reduced for any medications.

In addition to the usual risks associated with all medications that will be experienced by participants in both the control usual care group and the intervention group, participants in the intervention group are at risk of being exposed to or experiencing:

- i. Errors in switching to medications on the list of essential medications
- ii. Dissatisfaction with the new medications
- iii. Discontinuation effects of medications at the conclusion of the study

The risk of medication errors will be mitigated by having the pharmacist receiving the prescribed medication order review the electronic medical record which includes the history of medications previously prescribed. The pharmacist will use defined daily doses (DDD) defined by the WHO, which is a widely accepted standard for converting doses of equivalent

medications (these types of substitutions are currently routine for hospitalized patients).[32] The patients will also be contacted about the change in medications. Errors will thus only effect the medications taken by patients if they are made by prescribers and missed by both the pharmacist and the patient. Medication errors will be monitored by the Data and Safety Monitoring Board (DSMB).

In some cases, patients will be switched from brand name to generic products. Despite clear evidence that generics and brand name medications have similar clinical effects [33, 34], there is a perception by some that generics are inferior.[35] A RCT of “apparent” drug substitution (all pills were placebos) found that switching participants to placebos labeled as generic from branded placebos was associated with increased side effects such as dizziness, headache and dry mouth.[36] Medication adverse effects will be monitored by the DSMB.

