#### *Exclusion criteria*

- Valid public medication insurance (Ontario Drug Benefit) card.
- Family member living at same address of patients already enrolled.
- Joined practice within last 6 months.

We will exclude patients who are new to the practice as patients joining the practice in order to participate in the study is a potential source of bias and because some secondary outcomes require baseline assessments that will not be available for new patients.

We will not exclude patients who are eligible for public medication insurance but who do not have such coverage (e.g. patients who have lost or cannot access their benefit card).

We will not exclude patients with private medication insurance as long as they answer “yes” to the first question in the inclusion criteria. 7 % of Canadians who have medication coverage still report cost-related nonadherence.[5] Private insurance often requires some out of pocket expenses. Individuals who have private insurance and are not experiencing cost-related barriers to medication adherence will not be enrolled as they will not meet the inclusion criterion.

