#### *2.11 What is the proposed sample size and justification?*

Based on previous studies [29, 48, 49] we expected that between 40% and 60% of patients in the control group will be appropriately adherent. We expect that at least 90% of patients in the intervention group will be compliant (i.e. accept the free medications offered in the intervention). We believe that a 10% absolute improvement in appropriate adherence (in the presence of non-compliance) is the minimal difference that is clinically important. Assuming a Type I error probability of 5%, a sample size of 392 per group is required to have 80% power to detect a 10% absolute difference in adherence for any control group adherence values between 40% and 60%. No inflation for drop-out is applied since drop-outs will be considered non-adherent. Based on previous trials we expect the drop-out rate to be approximately 5 %.[29, 48, 49]

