### **Outcomes**

*Primary outcome:* Proportion (%) of patients who appropriately adhered to all prescribed treatments (i.e. were adherent to all prescriptions deemed appropriate).

*Secondary outcome:*

1. Proportion (%) of prescriptions that are appropriate.
2. Proportion (%) of prescriptions that are adhered to.
3. HbA1c levels in patients with diabetes (adjusted for baseline).
4. Blood pressure in hypertensive patients (adjusted for baseline).
5. LDL cholesterol levels in patients taking a statin (adjusted for baseline).
6. Per capita healthcare costs.

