### **Primary outcome**

The primary analysis will be performed on an intention to treat basis. All patients can be included since drop-outs or withdrawals will be considered non-adherent. Appropriate adherence will be compared using a chi-square test and the unadjusted treatment effect will be expressed as the absolute risk difference with 95% confidence interval. For the primary analysis a p-value of  $<0.05$  will be sufficient to reject the null hypothesis of no difference. Adjusted analyses will employ logistic regression and the adjusted (conditional) treatment effect will be expressed as an odds ratio with 95% confidence interval. Participants prescribed no regularly taken medicines (those taking only as needed medicines) were considered nonadherent on the assumption that adherence data for regular medicines may have been missing; a sensitivity analysis was performed to assess the effect of this assumption.

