### **Secondary outcomes**

The first two secondary outcomes are binary at the level of prescription within patient. This will be aggregated to the patient level and logistic regression will be used to compare groups. HbA1C, blood pressure and LDL cholesterol are all continuous and measured at baseline and 9-12 months. An analysis of covariance (ANCOVA) model will be used (via linear regression) to provide the estimates of treatment effect adjusted for baseline values. Since these are all secondary analyses which are supportive or exploratory, no corrections for multiple testing will be applied and only patients with data will be included. However the ITT approach is

still followed as patients will remain allocated to their randomized groups irrespective of compliance.

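### The primary outcome and secondary outcomes 1 and 2 are analysed without any pre-randomisation medication covariate; naming one in the SAP would be a cheap, modest gain in precision

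*Supplement*

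**What the plan says.** Protocol section 1.2 (24-month version) asks whether the intervention increases appropriate prescribing and whether it will "Increase treatment adherence (regardless of whether prescriptions are appropriate". The SAP of 9 September 2019 turns these into secondary outcomes 1 and 2; the second is "Proportion (%) of prescriptions that are adhered to". In the same list the third is "HbA1c levels in patients with diabetes (adjusted for baseline", and blood pressure and LDL carry the same qualifier. The SAP's section on secondary outcomes gives those three an ANCOVA on the baseline value. For outcomes 1 and 2 it says only: "This will be aggregated to the patient level and logistic regression will be used to compare groups".

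For the primary outcome the SAP says: "Appropriate adherence will be compared using a chi-square test and the unadjusted treatment effect will be expressed as the absolute risk difference". It also promises adjusted logistic analyses but names no covariates. The one stated basis for choosing any, under Patient characteristics, is that demographic imbalances judged clinically important may be adjusted for in a secondary analysis.

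On what is on file before randomisation, protocol section 1.6 has the pharmacist "review the electronic medical record which includes the history of medications previously prescribed". Section 2.2 requires clinicians to enter all prescriptions in the electronic medical record (EMR). Section 2.5 excludes patients who joined within the last 6 months, partly "because some secondary outcomes require baseline assessments that will not be available for new patients". Section 2.9 already has the EMR audited for renewal timing and appropriateness.

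**The concern.** Success on the primary outcome is all-or-none: the patient must be adherent to every regular medicine and have no inappropriate prescription. Someone on six medicines has more ways to fail than someone on one, so the number of regular medicines at randomisation should predict the outcome. How well a patient renewed before randomisation may predict it too. Both can be read from a record the trial already audits, and both are fixed before allocation.

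Neither is a demographic variable, so the plan's only route to a covariate would not bring them in. Choosing covariates by observed imbalance also does not target prognostic strength, and it leaves the choice open until the data have been seen. What is at stake is the width of the confidence interval for the outcome that decides the trial and for two secondary questions.

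**Working it through.** **1. The plan's own sample size.** Protocol section 2.11 states: "Assuming a Type I error probability of 5%, a sample size of 392 per group is required to have 80% power", for a 10-point difference at control rates of 40% to 60%. Sidedness is not stated; I take two-sided. With 1:1 allocation and no continuity correction,

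n = [1.960·√(2·p̄·(1−p̄)) + 0.8416·√(p₁(1−p₁) + p₂(1−p₂))]² / (p₂−p₁)².

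At 45% v 55%: p̄ = 0.50, and n = [1.960·0.7071 + 0.8416·0.7036]² / 0.01 = (1.978)² / 0.01 = 391.3, so **392**. Other pairs need fewer: 388 (40 v 50 and 50 v 60), 376 (55 v 65), 356 (60 v 70). Power with 392 is 80.07% at 45 v 55 and higher at the other pairs. The stated figure is right for the unadjusted test, with almost no reserve at the least favourable rate.

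**2. What a covariate could add.** If a baseline measure has within-arm correlation r with the outcome, adjustment multiplies the variance of the risk difference by about 1 − r². The documents give no r, so every row below is an assumption. Unadjusted 95% half-width at 45% v 55%: 1.96·√(2·0.45·0.55/392) = 6.96 points.

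| Assumed r | 1 − r² | Power, 392 per arm | Equivalent n per arm | Half-width (points) |
|---|---|---|---|---|
| 0 | 1.00 | 80.1% | 392 | 6.96 |
| 0.2 | 0.96 | 81.7% | 377 | 6.82 |
| 0.3 | 0.91 | 83.7% | 357 | 6.64 |
| 0.4 | 0.84 | 86.5% | 330 | 6.38 |
| 0.5 | 0.75 | 90.0% | 294 | 6.03 |

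Simulating a baseline-stratified risk difference gave variance ratios of 0.96, 0.91–0.92 and 0.84–0.85 at r = 0.2, 0.3 and 0.4, in line with the formula. If only half the participants have a baseline value, the factor is 1 − 0.5r², and power is 81.9% at r = 0.3 and 85.1% at r = 0.5.

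**3. Number of medicines alone.** Simulated trials: 392 per arm, success rates near 45% v 55%, 1 to 8 or 1 to 5 regular medicines (uniform, assumed), all-or-none success, and a patient-level random effect on the logit scale. The SD of that effect sets how strongly a patient's medicines succeed or fail together. The adjusted model adds log number of medicines.

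| Between-patient SD (assumed) | Approximate gain in power |
|---|---|
| 0.8 | 4–5 points |
| 2 | 2–3 points |
| 4 | none |

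Typical runs at SD 0.8 went from 79% to 83% with 1 to 5 medicines and from 79% to 85% with 1 to 8, with Monte Carlo error of about 1 point. On the risk-difference scale at SD 0.8, the variance ratio was 0.90–0.93. That matches r of about √0.07 to √0.10, or 0.26 to 0.32, in the first table. It was 0.93–0.95 when 10% of patients in both arms were set to fail regardless.

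**4. Prior renewal timing.** Two features limit it.
- Six months holds 183/90, or about two, renewals at the default interval.
- Everyone enrolled reports cost-related non-adherence in the last 12 months, so prior adherence may vary little. If only 10% were adherent at baseline, the largest possible correlation of that binary measure with a 50% outcome is √(0.1·0.5/(0.5·0.9)) = 0.33.

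**5. Secondary outcomes 1 and 2.** Treated as patient-level proportions, the interval narrows by 1 − √(1 − r²): 4.6%, 13.4% and 28.6% at r = 0.3, 0.5 and 0.7. Again r is assumed.

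**The case against.** The strongest reply is that nothing is wrong. The chi-square is prespecified and valid, 392 per group is correct for it, and an unadjusted risk difference is on the same scale as the 10-point minimal important difference. An adjusted logistic analysis is already planned, with only its covariates left unnamed. The contrast with HbA1c, blood pressure and LDL is not an inconsistency either. Those are continuous and restricted to patients with a recorded baseline, whereas composite adherence has no full baseline counterpart. The benefit also rests on assumptions. The self-report item is a single question about a patient's regular medicines as a whole, so medicines may well succeed or fail together, and then the count predicts little. All of this stands, and it limits the point to an improvement.

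It does not remove the point. The number of regular medicines needs no baseline survey and is defined even when it is zero.

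Three stronger statements a reader might infer are not supported:
- That these are the only per-person outcomes without baseline adjustment. Per capita healthcare costs, secondary outcome 6, have none either.
- That the record holds a baseline adherence value for every participant. The missed-dose survey in protocol section 2.9 is described only at 9–12 and 21–24 months. People with a first prescription or only as-needed medicines, a group the SAP foresees, have no renewal history.
- That a baseline covariate would check whether clinicians' prescribing to controls drifted toward the list. It would not; that needs a separate before-and-after analysis in the control arm.

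**Conclusion.** The point holds as a modest efficiency improvement. The plan leaves out cheap, probably prognostic covariates from the primary analysis and from secondary outcomes 1 and 2, and its only rule for choosing covariates would not bring them in. The omission causes no bias, and the trial does not miss its stated power.

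For the primary outcome, the gain from the number of medicines is about 0 to 5 points of power. It rests on an assumed distribution of medicine counts and, above all, on the assumed within-patient correlation. The extra value of renewal history, and any gain for secondary outcomes 1 and 2, cannot be sized from the documents. That earlier prescriptions are on file for most participants follows from the 6-month rule and EMR prescribing; the documents give no count.

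**What to change.** In the SAP, whatever imbalance is observed:
- **Primary outcome.** Prespecify a logistic model with arm, number of regular medicines on the EMR at randomisation (zero allowed, with the functional form stated), and on-time renewal in the previous 6 months by the existing 18-day rule, with a category for no history. Report the standardised absolute risk difference with 95% CI alongside the chi-square result, and state which of the two decides the trial.
- **Secondary outcomes 1 and 2.** Add the patient's own EMR-derived pre-randomisation value (appropriateness or renewal adherence respectively), with the same no-history category.

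The cost is SAP wording and some extra abstraction, covering 6 months of earlier order dates and the appropriateness of earlier prescriptions, from records already being audited. The downside is an estimate that depends on a model, which is why the chi-square result should stay in the report.

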### *1.3 Why is a trial needed now?*

Over the past several decades, multiple reports have called for national Canada-wide pharmacare or a publicly funded medication system that incorporates a national formulary.[1, 14, 25, 26] Romanow's report concluded that a unified formulary is necessary for collective bargaining

efforts because some provinces and territories are too small to individually negotiate prices, are subject to intense lobbying efforts from the pharmaceutical industry, and are often pressured to make poor decisions based on decisions made by other provinces.[25] A national formulary has been argued to be necessary to improve access, reduce costs, improve practice and to allow the implementation of universal Canadian pharmacare. [1] Yet no such system exists in Canada.

Some health system leaders have recently expressed openness to policy change. In December of 2014 the Ontario Minister of Health wrote in a newspaper op-ed that he “put the issue of national pharmacare on the front burner at the meeting with [his] provincial, territorial, and federal colleagues” and that he “was encouraged by federal Health Minister Rona Ambrose’s commitment after raising the need for a national pharmacare program.”[27] The results of this trial may inform pharmacare policy discussions and they will be communicated directly to decision makers provincially and federally.

